### Data coordination and site management

Data coordination and site management services will be performed at the Cardiovascular Center of the Korea University Guro Hospital.

## Discussion

Endovascular revascularization is a minimally invasive therapy for the treatment of patients with femoropopliteal arterial disease who suffer from intermittent claudication or critical limb ischemia. Technology has rapidly evolved during the last decade and there is now a growing body of experience in the treatment of even complex cases [21]. However, the femoropopliteal artery remains a challenging area for endovascular treatment. During movements, various forces are exerted on this vessel. Therefore the use of intravascular stents in the femoropopliteal artery continues to be controversial due to the potential for compression and fracture. As mentioned previously, recent stent design improvements focus on decreasing stent fracture rates which can negatively impact patency rates by rearranging strut alignment.

### Rationale of randomized trials comparing two different generation stents

The factors associated with in-stent restenosis after stent implantation in femoropopliteal lesion have been known to be very various; patient characteristics, lesion characteristics, and so on. Recently, various self-expandable nitinol stents have been manufactured by many companies and they each claim that the design of their product is superior in terms of radial force, stent deformity or fracture, and deployment system. As aforementioned, several studies have shown that stent fracture might be associated with in-stent restenosis. Also geographic miss, due to stent elongation or jumping during stent deployment, may be associated with stent fracture and in-stent restenosis [22].

On the other hand, the design of self-expandable nitinol stents might be different depending on the time they were developed; first-generation nitinol stents (such as Luminexx™ and SMART™) showed a remarkably high rate of stent strut fracture [22]. A second generation of slotted tube nitinol stents has been developed. These stents have better flexibility by reducing the number of connections between cells or crowns and configuring the spiral orientation of these interconnections [23]. Several studies have reported that these nitinol stents are more fracture-resistant and more flexible, with some of them providing superior patency rate (such as Life™ and Everflex™) [22, 24].

However, an important limitation to their studies is that they were non-randomized studies of relative small sample size or were confined to *in vitro*. As of yet, a multicenter randomized controlled trial for direct comparison of stent fracture and primary patency between two different nitinol stents has not been done except for one study: SMART™ versus Luminexx stent (Super SL trial) [14]. SMART™ and Luminexx stents have been classified as first generation self-expandable nitinol stents. The Complete-SE stent (Figure 2A) of Medtronic company is different to the SMART™ CONTROL stent (Figure 2B) of Cordis company in that the configuration of interconnection of Complete-SE has peak-to-peak connection, fewer bridges (4 versus 6) and struts (24 versus 36), a larger cell size, and a more spiral orientation of interconnection, compared to the SMART™ CONTROL stent. On the other hand, the SMART™ CONTROL stent has the peak-to-valley bridge, more bridges, a smaller cell size, and inline interconnection. Medtronic have claimed Complete-SE has been configured to minimize cell-to-cell and bridge-to-bridge interaction, increasing the stent’s flexibility without compromising radial strength. We made the hypothesis that the design of the Complete-SE stent might be more fracture-resistant or effective for in-stent restenosis, compared with the SMART™ CONTROL stent.

**Figure 2 Fig2:**
[figure not shown]
**Comparison for stent design. A**; Complete-SE stent design, **B**; SMART™ CONTROL stent design. Complete-SE stent is different to SMART™ CONTROL stent in that the configuration of interconnection of Complete-SE has peak-to-peak connection, fewer bridges (4 versus 6) and struts (24 versus 36), a larger cell size, and a more spiral orientation of interconnection, compared to the SMART™ CONTROL stent. On the other hand, the SMART™ CONTROL stent has the peak-to-valley bridge, more bridges, a smaller cell size, and inline interconnection.

### Rationale of randomized trials comparing clopidogrel and cilostazol following femoropopliteal stenting

To date, in many previous reports, dual antiplatelet therapy consisting of aspirin and clopidogrel has proven to decrease the incidence of cardiovascular death, myocardial infarction, and revascularization without an increase in major bleeding in patients who have undergone PCI regardless of stent type (bare metal stent or drug-eluting stent) [25–27]. In 2011 the ESC guidelines recommended dual antiplatelet therapy with aspirin and a thienopyridine such as clopidogrel for at least one month after infra-inguinal bare metal stent implantation (Class I, Level C). However, there has been no definite evidence or guideline for the optimal antiplatelet agent after stent implantation beyond one month later [17]. There have been many studies for the efficacy of thienopyridines in peripheral arterial disease. In the Swedish Ticlopidine Multicenter Study (STIMS) 687 patient of intermittent claudication were treated with ticlopidine or placebo, and the incidence of fatal or non-fatal myocardial infarction and stroke was reduced in the ticlopidine group [28]. A randomized blinded trial of clopidogrel versus aspirin in patients at risk of ischemic events (CAPRIE) demonstrated that clopidogrel was better in treating peripheral artery disease than aspirin (relative risk reduction in composite end point: 23.8%) [29]. Based on this trial, clopidogrel has been approved for prevention of ischemic events in patients with peripheral artery disease by the United State Food and Drug Administration [29]. Clopidogrel is effective in reducing cardiovascular events in a subgroup of patients with symptomatic peripheral arterial disease, with or without other clinical evidence of cardiovascular disease [11]. In the CHARISMA (Clopidogrel for High Atherothrombotic Risk and Ischemic Stabilization, Management, and Avoidance) trial, the large number of patients with documented prior myocardial infarction, ischemic stroke, or symptomatic peripheral artery disease appeared to derive significant benefit from dual antiplatelet therapy with clopidogrel plus aspirin beyond aspirin alone [30]. In the CASPAR (Results of the randomized, placebo-controlled clopidogrel and acetylsalicylic acid in bypass surgery for peripheral arterial disease) trial, the combination of clopidogrel plus aspirin did not improve limb or systemic outcomes in the overall population of peripheral artery disease patients requiring below-knee bypass grafting [31]. Subgroup analysis suggests that clopidogrel plus aspirin confers benefit in patients receiving prosthetic grafts (Hazard ratio: 0.65; 95% CI: 0.45-0.95; *P* = 0.025) without significantly increasing risk of major bleeding [31]. With the potential benefit of cilostazol on vascular function *in vitro*, there have been several previous efforts to prove the efficacy of cilostazol in patients undergoing endovascular therapy or stent implantation in peripheral arterial disease. For example, Soga *et al*. and Iida *et al.* have reported that cilostazol may improve amputation-free survival and limb salvage rate after endovascular therapy for infrainguinal disease in patients with critical limb ischemia and intermittent claudication [19, 32–34]. Also, they have demonstrated that cilostazol reduced restenosis after superficial femoral artery stenting with a self-expandable nitinol stent and it seems to be more effective in patients who are at a high risk of restenosis [35]. However, very few trials have not effectively or properly addressed the direct comparison for the efficacy and safety between clopidogrel and cilostazol. This trial is designed to evaluate the efficacy and safety between aspirin plus clopidogrel versus aspirin plus cilostazol in patients undergoing stent implantation in femoropopliteal lesions.

In conclusion, we still do not know whether there is a difference in primary patency and stent fracture between two self-expandable nitinol stents with a different design (SMART™ CONTROL versus COMPLETE™-SE) in stenotic or occlusive femoropopliteal arterial lesions. Furthermore, the efficacy and safety between aspirin plus clopidogrel versus aspirin plus cilostazol in patients undergoing stent implantation in femoropopliteal lesions will be evaluated. We hope to address these issues in the SENS-FP trial, whereby we will enroll a large unselected population of patients treated with stent implantation for significant peripheral arterial disease.

## Trial status

Recruitment is ongoing.

## Appendix

### Endpoints definitions

Binary restenosis: defined as a reduction in the luminal diameter of >50% according to the worst angiographic view at the narrowest site within the treated segment plus the 10-mm segments proximal and distal to the treated segment by catheter angiography or PSVR ≥2.5 (PSVR = peak systolic velocity within the area of stenosis divided by peak systolic velocity in a normal adjacent proximal artery segment) or total occlusion by duplex ultrasound. Stent fracture rate according fracture grade (minor, moderate, severe) [12]: plain X-ray examinations for the stent fracture are used or performed using at least two different angulations (30 to 45° difference) and the highest available magnification. Stent fracture is classified as minor (single strut fracture), moderate (fracture of more than 2 struts), or severe (complete separation of stent segments). Target lesion revascularization (TLR): defined as any repeat percutaneous intervention of the target lesion or bypass surgery of the target vessel performed for restenosis because of a return of ischemic symptoms, decrease of at least 1 Rutherford category, decrease in the ankle brachial index of >0.15, or restenosis of >50% as measured by catheter angiography. The target lesion is defined as the treated segment from 10 mm proximal to the stent and to 10 mm distal to the stent. Target extremity revascularization (TER): defined as any repeat percutaneous intervention of the target extremity or bypass surgery of the target extremity performed for restenosis because of a return of ischemic symptoms, decrease of at least 1 Rutherford category, decrease in the ankle brachial index of >0.15, or restenosis of >50% as measured by catheter angiography. Limb salvage: defined as survival free of amputation. Amputation is defined as above-ankle amputation of the index limb. Sustained clinical improvement rate [36, 37]: defined as persistent ABI value ≥0.15 and persistent improvement of ≥1 class according to Rutherford throughout follow-up when compared with baseline without the need for repeat TLR in surviving patients. Late loss: defined as a change in MLD from final angiogram to follow-up. Major adverse cardiac events (MACE): defined as composite of all-cause death, myocardial infarction, cerebrovascular stroke, and target lesion revascularization.

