## Method/Design

### Study objectives, hypothesis and design

The primary purpose of our study is to examine and compare the incidence of stent fracture and primary patency between two different nitinol stents (SMART™ CONTROL versus COMPLETE™-SE) in stenotic or occlusive femoropopliteal arterial lesions. The secondary purpose is to ascertain whether there is difference in efficacy and safety between aspirin plus clopidogrel versus aspirin plus cilostazol in patients undergoing stent implantation in femoropopliteal lesions. This is a prospective, randomized, multicenter trial to assess the efficacy of the COMPLETE™-SE versus SMART™ CONTROL stent by provisional stenting after balloon angioplasty for stenotic or occlusive femoropopliteal arterial lesions. The protocol of the trial has been registered with the National Institutes of Health Clinical Trials Registry (registration number: NCT01570803) and a brief flow chart of the whole study is summarized in Figure 1.

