### Outcome measures

The primary endpoint of this study is the rate of binary restenosis (stenosis of at least 50% of the luminal diameter) or PSVR (peak systolic velocity ratio) ≥2.5 or 0 (PSVR = peak systolic velocity within the area of stenosis divided by peak systolic velocity in a normal adjacent proximal artery segment) in the treated segment at 12 months after the intervention as determined by catheter angiography or duplex ultrasound. The secondary endpoints are as follows: 1) composite of binary restenosis and major stent fracture (moderate or severe stent fracture); 2) stent fracture rate according to fracture grade (minor, moderate, severe); 3) limb salvage rate free of above-the-ankle amputation; 4) sustained clinical improvement rate at 12-month follow-up; 5) repeated target lesion revascularization (TLR) rate; 6) repeated target extremity revascularization (TER) rate; 7) total reocclusion rate; 8) comparison of angiograph variables consisting of late loss and restenosis rate; 9) ankle-brachial index (ABI) at 12 months; 10) the rate of major adverse cardiovascular events (MACE) composed of all-cause death, myocardial infarction, repeat percutaneous coronary intervention (PCI), and stroke at 12 months; 11) incidence of geographic miss during stent deployment due to jumping and/or elongation; 12) rate of binary restenosis or PSVR ≥2.5 or 0 according to clopidogrel and cilostazol; and 13) major bleeding rate between clopidogrel and cilostazol group. The detailed definitions are summarized in the Appendix.

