### Statistical analysis

#### Sample size calculation

From previous studies, including ABSOLUTE [7], FAST [8], and ASTRON [9], recurrence rates in femoropopliteal lesions after one year were 32%, 34.4%, and 37%, respectively - approximately 35% on average. The recurrence rate for the SMART™ CONTROL stent was 34.8% in the SUPER-SL study - a multicenter, randomized controlled trial that compared two self-expanding nitinol stents, the SMART™ CONTROL and Luminexx stents, in femoropopliteal lesions [14]. So far, there are limited data on the one-year primary patency rate of the COMPLETE™-SE stent. Based on previous research results, the SMART™ CONTROL stent group will be the control group, and the COMPLETE™-SE stent group will be the experimental group. Based on the SUPER-SL results, the one-year primary patency of the SMART™ CONTROL stent is estimated to be 65% and the one-year primary patency of the COMPLETE™-SE stent is estimated to be 80%, which is higher than that of the SMART™ CONTROL stent. Recurrence will be defined as more than 50% restenosis or total occlusion under invasive angiography, or if invasive angiography is not performed, PSVR ≥2.5 when evaluated with duplex ultrasound. The statistical significance level is set at 5%, the power of test is set as 80%, and the randomization ratio is set as 1:1. Test for proportion and chi-square method are used. Using standard sample size formula, it was calculated that 138 patients per group are needed for a total of 346 patients, after accounting for a 20% dropout rate.

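### The stent fracture grades leave a fracture of exactly two struts, without separation, in no class; secondary endpoints 1 and 2 are affected

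*Protocol article*

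**What the plan says.** The appendix of the protocol article (Endpoints definitions) sets three fracture grades, with a citation to a published scale: "minor (single strut fracture), moderate (fracture of more than 2 struts), or severe (complete separation of stent segments".

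Two secondary endpoints under Outcome measures use these grades:

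- Endpoint 1 is the "composite of binary restenosis and major stent fracture (moderate or severe stent fracture". The line between minor and moderate is therefore also the line between non-major and major fracture.
- Endpoint 2 is the "stent fracture rate according to fracture grade (minor, moderate, severe". It has no residual or unclassified category.

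The section on objectives, hypothesis and design gives the primary purpose as to "examine and compare the incidence of stent fracture and primary patency between two different nitinol stents". The primary endpoint itself is binary restenosis at 12 months.

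**The concern.** A grading rule for an endpoint should place every possible finding in exactly one class. This one moves from one strut to more than two, and the missing case lies on the boundary that decides whether a fracture is major.

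Two things can then happen to a film showing two broken struts and no separation. If the wording is followed, the patient has a documented fracture with no grade. If the reader repairs the wording, there are two natural repairs: stretch minor to cover up to two struts, or read moderate as two or more. These give opposite answers for major fracture, and different readers or sites may choose differently. A choice made after films have been read would be a post hoc decision about who had a major fracture.

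Endpoints 1 and 2 are the only listed endpoints that measure fracture, and the discussion puts forward greater fracture resistance as part of the hypothesis for the COMPLETE-SE stent.

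**Working it through.** **1. The plan's own figure.** The only calculated figure is the sample size for restenosis. The inputs, from Sample size calculation, are: "the one-year primary patency of the SMART™ CONTROL stent is estimated to be 65" percent, "the one-year primary patency of the COMPLETE™-SE stent is estimated to be 80" percent, and "The statistical significance level is set at 5%, the power of test is set as 80%, and the randomization ratio is set as 1:1". Restenosis is then 0.35 versus 0.20, with mean 0.275 and difference 0.15. For a two-sided test without continuity correction:

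n = [1.960 × √(2 × 0.275 × 0.725) + 0.842 × √(0.35 × 0.65 + 0.20 × 0.80)]² / 0.15² = (1.238 + 0.524)² / 0.0225 ≈ 138 per group.

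With 20% dropout, 138 / 0.80 = 172.5, rounded up to 173 per group and 346 in total. The stated figures reproduce. They do not involve fracture, so the gap changes nothing here. They supply the two denominators used below: 138 evaluable and 173 enrolled per arm.

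**2. The grades applied literally.**

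| Fractured struts | No complete separation | Complete separation |
|---|---|---|
| 1 | minor | severe |
| 2 | **no class** | severe |
| 3 or more | moderate | severe |

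Exactly two struts without separation is the only empty cell. Three or more struts with complete separation fits the wording of both moderate and severe. It is taken here as severe, and either grade is major.

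**3. Number of ungraded patients.** The article gives no fracture rate and no distribution of strut counts, so both are assumed: 10–20% of patients have a fracture (f), and 10–30% of fractures involve exactly two struts without separation (s). Ungraded patients per arm = N × f × s.

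| | f = 0.10, s = 0.10 | f = 0.20, s = 0.30 |
|---|---|---|
| Share of patients | 1% | 6% |
| N = 138 | 138 × 0.01 = 1.4 | 138 × 0.06 = 8.3 |
| N = 173 | 173 × 0.01 = 1.7 | 173 × 0.06 = 10.4 |

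With a lower fracture rate of 5% and s = 0.10, the counts are 138 × 0.005 = 0.7 and 173 × 0.005 = 0.9.

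**4. Number missing from the composite.** Endpoint 1 is read in the usual way, as either component occurring. A two-strut patient with restenosis still counts, so the loss is N × f × s × (1 − r), where r is the restenosis risk in these patients. At the planning value r = 0.35, with N = 138, this is 1.38 × 0.65 = 0.9 to 8.28 × 0.65 = 5.4 per arm. With r from 0.20 to 0.50, it runs from 1.38 × 0.50 = 0.7 to 8.28 × 0.80 = 6.6. These patients are missing only if the intended grade for two struts is moderate. If it is minor, the composite loses nobody and only the grade rates are affected.

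**The case against.** The strongest reply is that this is a narrow wording slip in a condensed article. The scale is credited to a published source, which may be complete. The Clinical Event Adjudication Committee is to set explicit categorisation rules at the start of the trial. Two secondary endpoints out of 13 are touched.

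Much of this stands as a limit on the consequence, but it does not close the gap. The article states the definition in full, so this is not a detail left to another document. The committee's criteria are to be based on the protocol, and its section does not mention fracture films. A citation does not settle a case when the rule as printed omits it.

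Several stronger readings are tempting, but the documents do not support them:

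- *All two-strut fractures drop out of the composite.* They do not. Patients with restenosis still count, and complete separation makes the fracture severe. The article's background also reports fracture as closely related to restenosis, so the overlap may be considerable.
- *Half of the primary purpose is compromised.* That purpose names the incidence of fracture. An any-fracture count taken from the films includes two-strut fractures whatever their grade.
- *Readers cannot be masked, so discretion will favour one stent.* The article describes the COMPLETE-SE as having "fewer bridges (4 versus 6) and struts (24 versus 36" respectively, but as a design description. It does not say who reads the films, whether they are masked, or whether the designs can be told apart on X-ray.
- *The gap is as large as the between-stent difference in major fracture.* The article gives no such difference. A per-arm count is also not a bias: the same wording applies to both arms, and bias depends on how differently they are affected.

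**Conclusion.** The grading rule is wrong as written, for secondary endpoints 1 and 2 only. A fracture of exactly two struts without separation has no class. Followed literally, it is missing from all three grade rates and is not a major fracture. Graded ad hoc, it can land on either side of the major cut-off.

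Under the assumed rates, about 1.4 to 8.3 of 138 evaluable patients per arm would be ungraded (1.7 to 10.4 of 173 enrolled), and fewer would be missing from the composite. The lower denominator is the better guide, since ungraded films arise only in patients who have follow-up X-rays; it carries the plan's 20% dropout allowance over to those films. None of these rates comes from the documents, and a different fracture rate or two-strut share would scale the counts in proportion.

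The primary endpoint, its test and the sample size stand, as does an any-fracture incidence counted from the films. A reader might infer that two struts must be moderate, but the article does not show this.

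**What to change.** Before films are graded, restate the three grades under Endpoints definitions so that they are exhaustive and mutually exclusive. The sponsor should check the placement of two struts against the scale it cites. One form would be: minor, one strut; moderate, two or more struts without complete separation; severe, complete separation. If the cited scale places two struts in minor, the boundary moves accordingly; either choice closes the gap.

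Apply the same rule to major fracture in secondary endpoint 1, and re-code any two-strut films already read under the present wording.

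The cost is one wording change and possibly the re-coding of a few films. Recruitment is reported as ongoing, so the change can still be made before most films are read. No sample size, test or primary analysis changes.

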### Study population

Patients at least 20 years of age who have moderate or severe intermittent claudication or critical limb ischemia (Rutherford score of 2 to 6, except any patient who has undergone or plans to take major amputation) will be screened for study enrollment. A patient will be enrolled if they meet all of the inclusion and have none of the exclusion criteria. Inclusion criteria consist of clinical and anatomical criteria. The clinical criteria includes symptomatic peripheral-artery disease with moderate to severe claudication (Rutherford score of 2 to 3), chronic critical limb ischemia with resting ischemic pain (Rutherford score of 4), or chronic critical limb ischemia with ischemic ulcers (Rutherford score of 5 to 6), and patient must provide written informed consent. The anatomical criteria includes stenosis of more than 50% of, or occlusion of the ipsilateral femoropopliteal artery, patent (≤50% stenosis) ipsilateral iliac artery, or concomitantly treatable ipsilateral iliac lesions (≤30% residual stenosis), and at least one patent (less than 50% stenosis) tibioperoneal run-off vessel. Patients meeting any of the following criteria will be excluded from the study: failure to provide written informed consent; a history of major bleeding within prior two months; known hypersensitivity or contraindication to any of the following medications: heparin, aspirin, clopidogrel, cilostazol, or contrast agent; acute limb ischemia; previous bypass surgery or stenting of the ipsilateral femoropopliteal artery; untreated inflow disease of the ipsilateral pelvic arteries (>50% stenosis or occlusion); patients who have undergone major amputation (amputation of above the ankle) or major amputation is planned or required; patients with a life expectancy of less than one year due to comorbidities.

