All ipsilateral iliac arterial lesions should be treated with angioplasty and/or stenting concomitantly and residual stenosis should be less than 50%. Treatment of tibioperoneal lesions is recommended only in cases of critical limb ischemia. There should exist at least one patent (<50% stenosis) tibioperoneal run-off vessel with good antegrade flow.

A final angiography will be performed after the intervention in both groups, with the use of the same angles and magnifications used in the baseline angiograms. Simultaneously, reference vessel diameter (RVD), minimal luminal diameter (MLD), percent diameter stenosis, and acute gain should be measured. The reference vessel diameter will be obtained from averaging 5-mm segments proximal and distal to the lesion. Technical success will be defined as the successful access and deployment of the stent and less than 30% diameter residual stenosis after the revascularization.

For the post-procedural medication, aspirin 100 mg and clopidogrel 75 mg will be administered once daily for one month. Then, patients of each group will be randomized by web-based randomization to receive either clopidogrel 75 mg or cilostazol 100 mg once daily in addition to aspirin 100 mg for at least 11 months in a 1:1 manner.

After enrollment and index procedure, clinical follow-up will be planned at 1, 6, and 12 months to evaluate clinical outcomes and ankle-brachial index score. Also, all patients will be recommended to have a follow-up catheter angiography or duplex ultrasound at 12 months according to local clinical practice. The incidence of stent fracture and binary patency will be assessed by plain X-ray and quantitative femoral angiography. The investigators will be urged to follow up on patients, either by office visits or by telephone contacts, as necessary. Patient adherence to the study drug and side effects will be checked and monitored at every outpatient visit. The decision of drug discontinuation will be discussed and checked under the physician’s recommendation.

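### TLR and TER can count procedures prompted only by stenosis on scheduled angiography, and their Rutherford criterion runs in the wrong direction

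*Protocol article*

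**What the plan says.** In the Protocol article, Appendix, Endpoints definitions, TLR is "any repeat percutaneous intervention of the target lesion or bypass surgery of the target vessel performed for restenosis because of a return of ischemic symptoms", followed by three further alternatives: "decrease of at least 1 Rutherford category", a fall in ankle-brachial index (ABI) of more than 0.15, "or restenosis of >50% as measured by catheter angiography". TER has the same list, applied to the limb: "any repeat percutaneous intervention of the target extremity or bypass surgery of the target extremity performed for restenosis because of a return of ischemic symptoms".

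Under Randomization and interventions, "all patients will be recommended to have a follow-up catheter angiography or duplex ultrasound at 12 months according to local clinical practice".

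Outcome measures lists TLR and TER as secondary endpoints 5 and 6. Two other endpoints depend on TLR. Sustained clinical improvement requires that no repeat TLR was needed. MACE in the Appendix is a "composite of all-cause death, myocardial infarction, cerebrovascular stroke, and target lesion revascularization", whereas MACE in Outcome measures lists repeat coronary intervention and omits TLR.

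Study population fixes the direction of the Rutherford scale: 2 to 3 is claudication, 4 is rest pain, and the top is "chronic critical limb ischemia with ischemic ulcers (Rutherford score of 5 to 6").

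**The concern.** A revascularization endpoint is usually read as a measure of who needed treatment again. Here a patient with no symptoms, no Rutherford change and no ABI change counts once re-treated for an angiographic finding, and the protocol itself recommends imaging that can produce that finding. Part of TLR and TER may then reflect imaging practice and the readiness to treat silent stenosis, which can vary between sites. Sustained clinical improvement inherits this, as does MACE under the Appendix definition.

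The Rutherford criterion is a separate defect in the same sentences. Taken literally, an improvement of one category is a reason for a counted procedure and a worsening of one category is not. The same Appendix treats improvement of at least one category as clinical success.

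**Working it through.** **Reading the definitions.** The event is a procedure, not a scan, and the reasons are joined by *or*. For a patient at month 12 with no symptoms and no Rutherford or ABI change:

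| Finding and action | Counted as TLR? |
|---|---|
| Angiography shows >50% stenosis, not re-treated | No |
| Angiography shows >50% stenosis, re-treated for it | Yes |
| Duplex PSVR ≥2.5, not re-treated | No, although it is binary restenosis |
| Duplex PSVR ≥2.5, re-treated, with >50% stenosis measured by catheter angiography | Can count |

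Duplex is not itself a listed trigger, but a duplex-positive patient can reach the clause through a later angiogram.

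**Rutherford direction.** Study population orders the categories from claudication (2-3) through rest pain (4) to ulcers (5-6). A decrease is therefore an improvement. This needs no assumption, and the wording occurs in both definitions.

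**The plan's own figure.** Sample size calculation gives patency of 65% and 80%, alpha 5%, power 80% and 1:1 allocation. With a two-sided test and pooled variance under the null:

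- n = [1.960 × √(2 × 0.725 × 0.275) + 0.842 × √(0.65 × 0.35 + 0.80 × 0.20)]² / 0.15² = 137.9, so 138 per group.
- 138 / 0.80 = 172.5, so 173 per group and 346 in total.

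The stated figures reproduce. They rest on binary restenosis, so this point does not affect them.

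**Illustrative size.** The documents give no TLR rate, no angiography share, no silent share and no share of silent stenoses treated. All four are assumed below. Mean restenosis is (35% + 20%) / 2 = 27.5%, and evaluable patients are 2 × 138 = 276.

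*Number of imaging-only TLRs* = patients × restenosis × share with angiography × share silent × share treated:

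- Restenoses: 276 × 0.275 = 75.9.
- Low: 75.9 × 0.30 × 0.30 = 6.8 silent and found; × 0.25 treated = 1.7.
- High: 75.9 × 0.70 × 0.50 = 26.6 silent and found; × 0.75 treated = 19.9.

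*Spurious arm difference with equal true restenosis* = difference in angiography use × restenosis × share silent × share treated:

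- 0.15 × 0.275 × 0.40 = 1.65 points if every silent stenosis found is treated.
- × 0.25 = 0.4 points; × 0.75 = 1.2 points. In an arm of 138 this is 0.6 to 1.7 patients.
- With angiography use of 40% versus 60% and half of restenoses silent: 0.20 × 0.275 × 0.50 × (0.25 to 0.75) = 0.7 to 2.1 points.

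*Against sampling error.* If TLR is 10% to 30% (assumed), the standard error of the difference is √(2 × 0.10 × 0.90 / 138) = 3.6 points to √(2 × 0.30 × 0.70 / 138) = 5.5 points.

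**The case against.** The strongest defence is that an all-cause TLR with listed indications is an explicit and usable definition, and that preferring clinically driven TLR is a choice, not the correction of an error. That stands, and is why the stated endpoint should be kept. It can also be said that the definition cannot be applied without knowing the indication, and that the event committee is charged with setting criteria and minimum data. That is fair for the data field. But the committee's criteria are based on the protocol, so it inherits the stenosis-only route and the Rutherford wording.

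A reader might infer several stronger things that the documents do not support:

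- *That the 12-month angiogram creates events.* It does not. A repeat procedure must follow.
- *That a patient sent for duplex would escape being counted.* Not if re-treatment follows and catheter angiography measures more than 50% stenosis.
- *That an operator who knows the stent picks the modality.* The text refers only to local practice. Site custom under 1:1 randomization has no expected imbalance between arms.
- *That 7 to 27 events or 1.65 points are at stake.* Those figures require every silent stenosis found to be re-treated.
- *That MACE is affected outright.* TLR enters MACE in the Appendix but not in Outcome measures.

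The Rutherford wording may be called an obvious slip, since it sits beside returning symptoms and a falling ABI. The intended meaning is indeed easy to guess. It is still wrong as written in two endpoint definitions.

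**Conclusion.** The point holds in limited form. The stenosis-only route and the wrong Rutherford direction follow from the text without any assumption. The consequence of the first is mainly extra non-clinical events and between-site noise in TLR, TER and sustained clinical improvement. Bias between stents, or between drugs, arises only if angiography use or the decision to re-treat differs by arm, and nothing in the documents shows that either would.

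The size is conjectural: about 0.4 to 1.2 points under a 15-point difference in angiography use, 40% silent and 25-75% treated. That is a fraction of one standard error. Procedures prompted by the 12-month scan also fall at the edge of the window, so how many count depends on a cut-off that the article does not give. The reason to act is that the secondary endpoints become easier to interpret at little cost.

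**What to change.** 1. In both the TLR and the TER definition, replace the fall in Rutherford category with a worsening (rise) of at least one category.
2. Keep TLR and TER as stated. Record the indication for each event and pre-specify an additional analysis of clinically driven TLR and TER, meaning procedures done for return of ischemic symptoms, Rutherford worsening of at least one category, or an ABI fall of more than 0.15.
3. Reconcile the two MACE definitions. Apply the same split to MACE only if the reconciled version contains TLR.

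This changes how events are classified, not who is re-treated. The cost is wording in two definitions, one case report form field, and fewer events, hence less precision, in the clinically driven analysis. The article reports recruitment as ongoing, so indications can still be recorded as procedures occur and need not be reconstructed afterwards.
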